**Discussion:**

The aim of this multicenter observational study is to evaluate the efficacy and safety of VT-ART, comparing the clinical outcome of patients undergone to VT-ART to patients not having received such a procedure. The two groups will not be collected by direct, prospective accrual to avoid randomization among the innovative and traditional arm: A retrospective selection through matched pair analysis will collect patients presenting features similar to the ones undergone VT-ART within the consortium (in each center independently). Our trial will enroll patients with optimized medical therapy in whom endocardial and/or epicardial radiofrequency ablation (RFA), the gold standard for VT ablation, is either unfeasible or fails to control VT recurrence. Our primary outcome is investigating the difference in overall cardiovascular survival among the group undergoing VT-ART and the one not exposed to the innovative procedure. The secondary outcome is evaluating the difference in ventricular event-free survival after the last procedure (i.e., last RFA vs. VT-ART) between the two groups. An additional secondary aim is to evaluate the reduction in the number of VT episodes comparing the 3 months before the procedure to the ones recorded at 6 months (from the 4th to 6th month) following VT-ART and RFA, respectively. Other secondary objectives include identifying the benefits of VT-ART on cardiac function, as evaluated through an electrocardiogram, echocardiographic, biochemical variables, and on patient quality of life. We calculated the sample size (in a 2:1 ratio) upon enrolling 149 patients: 100 in the non-exposed control group and 49 in the VT-ART group. Progressively, on a multicentric basis supervised by the promoting center in the VT-ART consortium, for each VT-ART patient enrollment, a matched pair patient profile according to the predefined features will be shared with the consortium to enroll a patient that has not undergone VT-ART.

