Other secondary objectives include identifying the benefits of VT-ART on cardiac function, as evaluated through an electrocardiogram, echocardiographic, biochemical variables, and patient’s quality of life.

In particular, we will evaluate the reduction or suspension of antiarrhythmic drug use compared to the baseline and the improvement of cardiac parameters (such as LVEF, left ventricular end-diastolic volume/diameter, ventricular strain, end-systolic volume/diameter, RVEF, and TAPSE for right ventricular function).

Analyzed biochemical variables will include heart failure biomarkers, such as NT-proB-type natriuretic peptide (NTproBNP), troponin (hs-TnI), and inflammation markers, such as polymerase chain reaction (PCR), tumor necrosis factor-alpha (TNF-alpha), and interleukin 6 (IL-6).

Improvement in the patient’s quality of life will be assessed compared to the pre-treatment period using the SF36 scale.

The patient’s QoL will be assessed before and after VT-ART using the SF36 scale (6); the post-treatment score will be compared to the pre-treatment period’s one to assess potential improvement. The post-treatment QoL evaluation will be performed at 3, 6, and 12 months after VT-ART. Once centers join the consortium, the SF36 QoL scale will be offered (although not mandatory) to all patients undergoing RFA: Before and at 6 months after conventional therapy.

Secondary outcome analyses will investigate the improvement of QoL scores after VT-ART and how QoL scores change the comparison between VT-ART and RFA.

Further secondary outcome analyses will be developed through imaging: Contrast infusion MRI and CT scan will be performed as required but not mandatory (if not contraindicated due to ICD) in the experimental arm.

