### Statistical considerations and sample size for matched pair analysis

A descriptive analysis will summarize the total number and stratification of patients with RFA and VT-ART.

We will perform a comparative analysis between RFA and VT-ART in patients with structural heart disease and refractory VT. Each patient who will be treated by VT-ART will be compared with two patients in the control group treated with RFA and best standard care but without VT-ART, on the basis of the following matching factors: Etiology of cardiomiopathy (ICM, NICM, and ACM), ventricular arrhythmia presentations (sustained ventricular tachycardia; incessant sustained ventricular tachycardia; and electrical storm), diagnostic tools used for scar definition (CT, MR, EAM, and ECG), arrhythmogenic focus anatomical intracardiac location (on the basis of VE exit by ECG and by activation map of VT), TA volume (endocardial electroanatomic substrate mapping area/volume in all cases; and epicardial mapping area/volume in case of 3D epicardial electroanatomic substrate mapping), heart volume, heart-to-TA volume, rate number of previous RFA attempts, type of previous RFA attempts (endocardial and epicardial), time (in days) between the first RFA attempt and VT-ART, time (in days) between the last RFA attempt and VT-ART, previous percutaneous stellate ganglion blockade, time (in days) between the percutaneous stellate ganglion blockade and VT-ART previous use of amiodaron, NYHA group, LVEF, BMI, age, and gender.

As mentioned, applied matching factors are summarized in Table 2.

Continuous data will be expressed as mean ± standard deviation, as appropriate, for all variables collected from the entire population or specific subgroups. A comparative analysis for subsequent levels of qualitative variables through the chi-square test and quantitative variables (scores on quality of life) with the *T*-test will be performed.

Non-parametric tests will be provided where the population distribution does not have a known form (normal Gaussian).

The differences in baseline and follow-ups between the same group will be analyzed with repeated measures approach: using the Friedman test and MANOVA for continuous variables and McNemar or Cochran’s *Q*-tests for categorical ones.

The significance of the tests is fixed with *p* < 0.05.

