#### Sample size

The calculation of the sample size considered followed assumptions:

-A total of 95% confidence level;-The drop-out rate of 10%;-Expected difference between the two treatments for 3-month and 6-month VT burden in terms of overall response rates: 20% higher in arm including VT-ART compared to the control group;-Power of 80%.

To improve clinically adequate balancing, we will enroll two matching paired patients in the group not undergoing VT-ART for each patient who undergoes VT-ART in a 2:1 ratio, favoring a larger proportion of patients not undergoing the innovative procedure (i.e., VT-ART).

Under these hypotheses, to detect a 20% improvement in the VT burden control rate in the VT-ART group vs. the control group, we calculated the sample size (in a 2:1 ratio) upon enrolling 149 patients: 100 in the non-exposed control group and 49 in the VT-ART group. Progressively, on a multicentric basis supervised by the promoting center in the VT-ART consortium, for each VT-ART patient enrollment, a matched pair patient profile according to the predefined features will be shared with the consortium to enroll two similar patients who have not undergone VT-ART. For enrollment into the control group, recruitment of clinical cases from retrospective case series within the multicentric consortium will also be allowed, with the only condition to be not earlier than 5 years from the enrollment of the matched pair patient in the VT-ART group (to avoid the possible influence of a too early approach for standard procedures).

All statistical analyses will be performed using SPSS^®^ version 25.0 software (©Copyright IBM Corporation 1994, 2017).

Due to the potential difficulty of enrolling the patients through the complete match of all matching factors, a protocol rule will be applied through patient’s collection.

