### Follow-up

Follow-up will be conducted for 36 months after treatment administration.

Patients prospectively enrolled within the consortium and treated by VT-ART will undergo ICD interrogations for up to 36 months after enrollment.

After a blanking period of 3 months, regular ICD interrogations [with intracardiac electrogram (EGM) storage of VT/VF or appropriate shock or ATP] will be prospectively collected for patients treated by VT-ART at 6, 9, 12, 18, 24, 30, and 36 months after the VT-ART procedure.

The ICD interrogation will collect the events along the last 3 months ahead of each follow-up evaluation.

Patients prospectively enrolled within the consortium and treated by RFA will undergo the same follow-up schedule if possible according to the clinical patient’s need and compliance.

Patient data retrospectively collected within the consortium and treated by either RFA or VT-ART will be retrospectively extracted at the same time points of prospective follow-up.

The final analysis will be performed only for patients with available data for the mentioned time points, either retrospectively or prospectively collected.

Quality of life will be assessed before the procedure (for prospectively enrolled patients candidate to VT-ART and RFA) and at 3, 6, and 12 months after therapy. Improvement in the patient’s quality of life will be assessed compared to the pre-treatment period using the SF36 scale.

Patient follow-up will thus, briefly, include:

•ICD interrogation (with EGM storage of VT/VF) at 6, 9, 12, 18, 24, 30, and 36 months from treatment.•A total of 12-lead ECG at 3, 6, and 12 months.•Echocardiography at 3, 6, and 12 months.•QoL assessment using the SF36 scale (7) will be performed at 3, 6, and 12 months for patients undergoing VT-ART.•QoL assessment using the SF36 scale will be performed at 6 months for patients undergoing RFA.

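### The SF36 schedule and status for RFA patients are stated inconsistently, and the planned VT-ART versus RFA quality-of-life comparison rests on voluntary RFA respondents at 6 months, without secured matched sets

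*Protocol article*

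**What the plan says.** **Objective and test.** Outcome measures says that secondary analyses will examine improvement after VT-ART and "how QoL scores change the comparison between VT-ART and RFA". The statistical considerations section plans a comparative analysis in which "quantitative variables (scores on quality of life) with the *T*-test will be performed", with non-parametric tests where normality fails and p < 0.05 as the threshold.

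**VT-ART schedule.** Outcome measures has SF36 before treatment, and then "The post-treatment QoL evaluation will be performed at 3, 6, and 12 months after VT-ART".

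**RFA schedule, stated three ways.**
- Outcome measures, applying once a centre has joined the consortium: "the SF36 QoL scale will be offered (although not mandatory) to all patients undergoing RFA: Before and at 6 months after conventional therapy".
- Follow-up, running text: assessment before the procedure, "for prospectively enrolled patients candidate to VT-ART and RFA) and at 3, 6, and 12 months after therapy".
- Follow-up, closing list: "QoL assessment using the SF36 scale will be performed at 6 months for patients undergoing RFA".

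**Source of controls.** The Discussion part of the abstract says "A retrospective selection through matched pair analysis will collect patients presenting features similar to the ones undergone VT-ART". The Sample size section adds: "For enrollment into the control group, recruitment of clinical cases from retrospective case series within the multicentric consortium will also be allowed", going back up to 5 years. The Protocol overview also allows VT-ART procedures delivered before the trial started.

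**The concern.** Two problems meet here. First, a centre reading the protocol cannot tell whether an RFA patient owes one or three post-procedure questionnaires, or whether they are required or merely offered. Second, a between-group comparison is announced although the two groups are measured under different rules: a scheduled assessment for VT-ART, a voluntary one for RFA.

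Matching is this observational study's main control of confounding. If SF36 exists only for those RFA patients who were seen after their centre joined and who chose to complete it, the respondents may differ from the matched controls as a whole. A T-test on whatever scores are available does not adjust for baseline and does not keep the matched sets together. A difference at 6 months could then reflect who answered rather than what treatment they received. A later analysis plan cannot recover questionnaires that were never collected.

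**Working it through.** **1. The schedules side by side**

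| Place | Group | Before | After | Status |
|---|---|---|---|---|
| Outcome measures | VT-ART | yes | 3, 6, 12 months | scheduled |
| Outcome measures | RFA | yes | 6 months | offered, not mandatory |
| Follow-up, running text | prospective VT-ART and RFA | yes | 3, 6, 12 months, not limited to VT-ART | no mention of optional |
| Follow-up, list | VT-ART | not listed | 3, 6, 12 months | will be performed |
| Follow-up, list | RFA | not listed | 6 months | will be performed |

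The bracket in the Follow-up text may belong only to the pre-procedure assessment. Even so, the 3, 6 and 12 months that follow are not restricted to VT-ART. The RFA schedule therefore conflicts within Follow-up, and the optional status conflicts between Follow-up and Outcome measures.

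**2. What can be compared under the Outcome measures schedule**

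Both groups share baseline and 6 months. Of the three post-procedure time points for VT-ART, two (3 and 12 months) have no RFA counterpart.

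**3. How many matched sets would have a measured control**

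The protocol states no sample size, SD or effect for SF36, so there is no quality-of-life figure to reproduce. It gives 49 VT-ART patients and 100 controls, matched 1:2. The retrospective share and SF36 uptake are not given. The values below are assumptions, with no SF36 in retrospective controls and availability independent between controls.

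Share of controls measured, p = (1 − retrospective share) × uptake:
- half retrospective, half uptake: p = 0.5 × 0.5 = 0.25
- three quarters retrospective, half uptake: p = 0.25 × 0.5 = 0.125

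Sets with at least one measured control, 1 − (1 − p)²:
- p = 0.25: 1 − 0.75² = 0.4375, about 44%
- p = 0.125: 1 − 0.875² = 0.234, about 23%

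Requiring both controls would give p²: 0.25² = 0.0625 (6%) and 0.125² = 0.016 (2%). A matched analysis can use a set with one measured control, so the first pair of figures is the relevant one.

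**4. Precision if sets are ignored**

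The detectable standardized difference is (1.96 + 0.84) × √(1/49 + 1/n), for two-sided 0.05, 80% power, all 49 VT-ART patients measured and n measured controls. Power is for an assumed difference of 0.5 SD.

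| Controls with SF36 | Detectable difference | Power for 0.5 SD |
|---|---|---|
| 100 | 0.49 SD | 82% |
| 75 | 0.51 SD | 78% |
| 50 | 0.56 SD | 70% |
| 25 | 0.69 SD | 53% |
| 10 | 0.97 SD | 30% |

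For n = 25: 2.80 × √(0.0204 + 0.04) = 0.69. The loss is gradual. The table describes precision only and says nothing about selection.

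**The case against.** The strongest reply is that a comparison can be made. Both groups have baseline and 6 months in Outcome measures, the Follow-up list confirms 6 months for RFA, and a test is named. This stands. A reader might infer that the quality-of-life comparison is impossible; the documents do not support that.

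A reader might also infer that retrospective controls have no SF36 at all, or that matching is lost for this endpoint. Neither is stated. Follow-up provides for retrospective extraction at the prospective time points, so a form completed in routine care could in principle be used. What the text supports is that no SF36 is planned for such patients: the RFA offer starts when a centre joins, and the pre-procedure assessment is tied to prospective enrolment. The same holds for retrospective VT-ART cases, so the gap is not confined to controls. Missing forms thin out the matched sets; they do not abolish matching.

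Nor do the documents show that RFA volunteers would be the fitter patients. Selection is a risk, and its direction is unknown.

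Finally, quality of life is one of several further secondary objectives, the sample size rests on VT burden, and the schedule conflict could be cured by editing one sentence. All true. But that edit would leave the optional status and the unadjusted test in place, and the protocol does announce the comparison.

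**Conclusion.** The concern holds in a limited form. The RFA schedule and status for SF36 contradict each other between Outcome measures and Follow-up and within Follow-up. Under the Outcome measures version, the VT-ART versus RFA comparison is limited to baseline and 6 months, in RFA patients who choose to take part, with no 3- or 12-month contrast and no assurance that matched sets stay intact.

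The extent depends on two quantities that the protocol does not give. Under the assumed shares, between about a quarter and a little under half of the 1:2 sets would have a measured control. These are illustrations and assume independence; higher uptake or fewer retrospective controls would improve them. The schedule conflict and the unequal measurement rules depend on no assumption. The primary endpoint is not affected. The point should be corrected before the comparative quality-of-life result is interpreted.

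**What to change.** 1. Reconcile Outcome measures and Follow-up to one SF36 schedule and one status for RFA patients, with baseline and 6 months as a standard assessment for prospectively enrolled RFA controls.
2. Define the between-group analysis as 6-month SF36 change adjusted for baseline, in prospectively enrolled patients, within matched sets that contain a measured VT-ART patient and at least one measured control. This replaces an unadjusted T-test on all available scores.
3. Report SF36 completion by group.
4. State that the 3- and 12-month VT-ART changes are descriptive and support no claim against RFA.

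Making the form standard acts directly on uptake. With half of the controls retrospective and full completion among the rest, p rises from 0.25 to 0.50 and usable sets from 44% to 1 − 0.5² = 75%. With three quarters retrospective, p rises from 0.125 to 0.25 and usable sets from 23% to 44%.

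The cost is protocol wording and a short questionnaire, already in use in the study, for prospective RFA controls. The comparative result will rest on a smaller, stated subset, because VT-ART patients without a measured control drop out of it.

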### Statistical considerations and sample size for matched pair analysis

A descriptive analysis will summarize the total number and stratification of patients with RFA and VT-ART.

We will perform a comparative analysis between RFA and VT-ART in patients with structural heart disease and refractory VT. Each patient who will be treated by VT-ART will be compared with two patients in the control group treated with RFA and best standard care but without VT-ART, on the basis of the following matching factors: Etiology of cardiomiopathy (ICM, NICM, and ACM), ventricular arrhythmia presentations (sustained ventricular tachycardia; incessant sustained ventricular tachycardia; and electrical storm), diagnostic tools used for scar definition (CT, MR, EAM, and ECG), arrhythmogenic focus anatomical intracardiac location (on the basis of VE exit by ECG and by activation map of VT), TA volume (endocardial electroanatomic substrate mapping area/volume in all cases; and epicardial mapping area/volume in case of 3D epicardial electroanatomic substrate mapping), heart volume, heart-to-TA volume, rate number of previous RFA attempts, type of previous RFA attempts (endocardial and epicardial), time (in days) between the first RFA attempt and VT-ART, time (in days) between the last RFA attempt and VT-ART, previous percutaneous stellate ganglion blockade, time (in days) between the percutaneous stellate ganglion blockade and VT-ART previous use of amiodaron, NYHA group, LVEF, BMI, age, and gender.

As mentioned, applied matching factors are summarized in Table 2.

Continuous data will be expressed as mean ± standard deviation, as appropriate, for all variables collected from the entire population or specific subgroups. A comparative analysis for subsequent levels of qualitative variables through the chi-square test and quantitative variables (scores on quality of life) with the *T*-test will be performed.

Non-parametric tests will be provided where the population distribution does not have a known form (normal Gaussian).

The differences in baseline and follow-ups between the same group will be analyzed with repeated measures approach: using the Friedman test and MANOVA for continuous variables and McNemar or Cochran’s *Q*-tests for categorical ones.

The significance of the tests is fixed with *p* < 0.05.

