## Populations

Our aim is to enroll patients with structural heart disease, in whom the presence of a myocardial scar induces refractory monomorphic VT or ventricular fibrillation (VF), as documented by either implantable cardioverter defibrillator (ICD) appropriate shocks or anti-tachycardia pacing (ATP) at ICD interrogation. We will enroll patients with recurrent VT/VF episodes despite optimal medical therapy (i.e., class III antiarrhythmic drugs) and at least one previous attempt of RFA or patients in whom ablation is not feasible, because of contraindications to the procedure or of patient intolerance. Previous percutaneous stellate ganglion blockade is neither a requirement for inclusion criteria nor exclusive criteria that will be collected in the standardized data collection for potential subgroup analysis.

Eligibility criteria are summarized in Table 1.

**TABLE 1 T1:** Inclusion and exclusion criteria.

Inclusion criteria	1. Patients with structural heart disease and monomorphic VT refractory to optimal medical therapy and previous RFA attempts (minimum of one attempt RFA)
	2. Patients with contraindications to conventional ablation or not suitable for any non-interventional approach, refusing any surgical ablative attempt; or patients who have already undergone RFA with arrhythmogenic focus refractory to previous ablation procedures
	3. Age >18 years
	4. Candidates not suitable for heart transplantation

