## Methods/design

Our trial will investigate the effects of administering a single fraction of external beam radiation delivered through SBRT techniques at a dose of 25 Gy on patients with recurrent episodes of VT and in whom optimal medical therapy and previous RFA attempts have failed to provide benefit from VT burden control. We will perform matched pair analysis with dynamic cohorts. We will compare two groups of patients: One that has been treated by all the standard approaches but has not undergone VT-ART and a second group that has also received VT-ART. The entire enrolled group (by multicentric recruitment) will be stratified according to some predefined characteristics and analyzed by matched pair analysis, based on the characteristics of patients treated with VT-ART. Once a patient is enrolled to undergo VT-ART within the multicentric consortium, the search for two patients with similar feature profiles not undergoing VT-ART will be shared.

Matching factors taken into account are summarized in Table 2.

**TABLE 2 T2:** Applied matching factors.

Parameter type	Subgroup options
Etiology of cardiomyopathy*	ICM
	NICM
	ACM
Age*	
Gender*	
BMI	
LVEF*	
NYHA group*	
Ventricular arrhythmia presentations*	Sustained ventricular tachycardia incessant sustained ventricular tachycardia electrical storm
Arrhythmogenic focus anatomical intracardiac location	Based on VE exit by ECG and by the activation map of VT
Diagnostic tools used for scar definition	CT
	MR
	EAM
	ECG
TA volume*	Endocardial electroanatomic substrate mapping area/volume in all cases; epicardial mapping area/volume in the case of 3D epicardial electroanatomic substrate mapping
Heart volume	cc range
Heart-to-TA volume	cc range
Previous use of amiodaron	Y/N
Number of previous RFA attempts*	
Type of previous RFA attempts	endocardial
	epicardial
Unfeasibility to repeat RFA	Y/N
Local recurrence of TA (same area of last RFA)	Y/N
Previous percutaneous stellate ganglion blockade	Y/N

TA, target area by electroanatomical mapping; BMI, body mass index; RFA, radiofrequency ablation; LVEF, left ventricle ejecting fraction; *mandatory matching factor.

Figure 1 depicts the design of the VT-ART study.

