## Discussion and final considerations

Sustained monomorphic VT is a potentially life-threatening condition that often affects patients with structural heart diseases. VT recurrence poses a severe threat to health and quality of life. Long-term management of recurring VT relies mainly on ICDs, pharmacological control (i.e., class III antiarrhythmic), and RFA of the pathological arrhythmogenic substrate.

New long-term solutions are currently being sought for patients in whom VT is refractory to conventional treatment strategies or in whom it cannot be performed. In patients with structural heart disease, the rate of VT recurrence after RFA has been reported to be between 25 and 50% (8). Intrinsic technical aspects of the procedure (e.g., difficult anatomical location of the arrhythmic substrate) as well as patient-related factors (e.g., patient frailty) may limit RFA feasibility in a portion of the population. Patients with structural heart disease are often fragile and have a varying number of comorbidities. Therefore, procedure invasiveness could be a limiting factor in the choice of the best treatment strategy (9).

Cuculich et al. first investigated the efficacy and safety of stereotactic radiation for the ablation of VT in a five-patient case series, which was later followed by the publication of a phase I/II prospective study by the same authors, including 19 patients (1, 2). Both studies reported a statistically significant reduction (99.9 and 94%, respectively) in VT episodes after a blanking period of 4 weeks. Subacute and chronic treatment-related side effects ranged from asymptomatic pericardial effusion to radiation-induced pericarditis and pneumonitis and were successfully treated with corticosteroids. Since then, a growing number of scientific articles have been published on this matter.

Overall, VT-ART has been proven to be an effective and adequately safe intervention in other studies (10, 11). Its non-invasive nature makes it a safe alternative for patients who are not suitable for percutaneous RFA (9). Nevertheless, despite the promising results detected by sporadic reports, limited case series, and systematic reviews (12), we still do not know if and at what level VT-ART (and STAR in general) could significantly and effectively improve the clinical scenario of such complex malignancies.

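### Neither matching list contains a comorbidity or frailty factor, although the protocol says frailty may limit who can have RFA, so the cardiovascular survival comparison can be biased, probably against VT-ART

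*Protocol article*

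**What the plan says.** In Discussion and final considerations, the protocol article states that "patient-related factors (e.g., patient frailty) may limit RFA feasibility in a portion of the population". It adds that "Patients with structural heart disease are often fragile and have a varying number of comorbidities" and concludes that "procedure invasiveness could be a limiting factor in the choice of the best treatment strategy".

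The section Populations admits, alongside patients in whom RFA has failed, "patients in whom ablation is not feasible, because of contraindications to the procedure or of patient intolerance". The statistical section compares each VT-ART patient with "two patients in the control group treated with RFA and best standard care but without VT-ART". Outcome measures makes cardiovascular survival the primary endpoint, counted from VT-ART in one group and from the last RFA in the other.

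Matching factors appear in two places. Table 2 (Methods/design) has 18, of which 8 are starred as mandatory. The list in the statistical section overlaps with it and ends with "previous use of amiodaron, NYHA group, LVEF, BMI, age, and gender". Table 2 alone has a yes/no item, "Unfeasibility to repeat RFA", without a star. Under Sample size, enrolment of controls may fall back to the starred factors only if full matching is too slow.

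**The concern.** The comparison is not randomised, and matching is the control of confounding that this document describes. A characteristic that steers patients away from RFA and also raises the risk of cardiovascular death should be balanced between the groups or handled in the analysis. The protocol names such a characteristic itself, but neither matching list includes it.

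The group definitions make an imbalance plausible. A control was able to undergo RFA at time zero, whereas some VT-ART patients were treated because they could not. If the VT-ART group is frailer, a real survival benefit could be diluted or hidden, or a null effect could look like harm. More patients would not cure this, because the bias does not shrink with sample size.

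**Working it through.** **Step 1: check the lists.** The 18 factors of Table 2 fall into these groups:
- Patient and cardiac status: etiology*, age*, gender*, BMI, LVEF*, NYHA*.
- Arrhythmia and substrate: arrhythmia presentation*, focus location, diagnostic tools, target-area volume*, heart volume, heart-to-target volume, local recurrence.
- Treatment history: amiodarone, number of RFA attempts*, type of RFA attempts, unfeasibility of repeating RFA, stellate ganglion blockade.

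The 8 mandatory factors are marked with an asterisk. None of the 18 is a renal, pulmonary, diabetes, comorbidity-score or frailty item. The list in the statistical section adds time intervals between procedures but no comorbidity item, and it leaves out the unfeasibility item.

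**Step 2: follow the proxy.** Under full matching by Table 2, the unfeasibility item is matched as yes/no, without a reason. Under the list in the statistical section it is not matched. Under the fallback it is not matched either, because it has no star; BMI is also dropped.

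**Step 3: illustrate the size.** The protocol gives no prevalence of frailty or comorbidity and no hazard ratio for it, so these inputs are assumptions. Let pA and pB be the prevalence of major comorbidity or frailty in the VT-ART and control groups, and H its hazard ratio for the endpoint. If VT-ART has no effect, the apparent hazard ratio at the start of follow-up is

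B = [1 + pA(H − 1)] / [1 + pB(H − 1)]

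| pA vs pB | H = 1.5 | H = 2 | H = 3 |
|---|---|---|---|
| 40% vs 25% | 1.200/1.125 = 1.07 | 1.40/1.25 = 1.12 | 1.80/1.50 = 1.20 |
| 50% vs 25% | 1.250/1.125 = 1.11 | 1.50/1.25 = 1.20 | 2.00/1.50 = 1.33 |
| 60% vs 20% | 1.300/1.100 = 1.18 | 1.60/1.20 = 1.33 | 2.20/1.40 = 1.57 |

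A true hazard ratio of 0.70 would appear as 0.70 × 1.07 = 0.75 at the low end and 0.70 × 1.57 = 1.10 at the high end.

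**Step 4: effect on the test.** Take the planned 49 VT-ART and 100 control patients, and assume 45 cardiovascular deaths (the protocol states no number) and B = 1.25 (for example 50% vs 20% with H = 2: 1.5/1.2). With Schoenfeld's approximation, the standardised effect is |ln HR| × √(45 × 49/149 × 100/149) = |ln HR| × 3.15.
- True HR 0.50, no bias: 0.693 × 3.15 = 2.18, power 59%.
- True HR 0.50, with bias (apparent 0.625): 0.470 × 3.15 = 1.48, power 32%.
- True HR 1.00, with bias: 0.223 × 3.15 = 0.70. The two-sided false-positive rate is about 11% instead of 5%, of which 10.4 points lie in the direction of harm.

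With 30 or 60 deaths instead of 45, that false-positive rate is about 9% or 13%. It rises with more events.

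**The case against.** Much of the case on the other side stands.

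- **Adjustment may exist elsewhere.** A reader might infer that the trial makes no adjustment for comorbidity. The article does not show that. It condenses a fuller protocol, and survival-model covariates are normally left to the analysis plan, which is not at hand. The point rests on the matching lists, which this document does fix.
- **Comorbidity may be collected.** A reader might also infer that the data are not recorded. The protocol refers to a standardised data collection and an electronic CRF, and neither is shown.
- **Matching and eligibility narrow the gap.** Age, NYHA, LVEF and number of RFA attempts are mandatory factors. NYHA IV, ongoing neoplastic disease, active ischaemia and LVADs are excluded, and life expectancy must exceed one year in the absence of VT. These limits remove the sickest patients. They mostly describe cardiac severity, however, and a one-year threshold does not balance prognosis over 36 months.
- **The proxy does some work.** Under full matching by Table 2, a VT-ART patient who cannot repeat RFA is paired with controls coded the same way. It would be wrong to say that perfect matching leaves the whole imbalance. But the item gives no reason, such a control still had an RFA at time zero, and the fallback loses the item.
- **The wording in the Discussion is hedged.** Frailty may limit RFA in some patients, and technical reasons such as a difficult location are named too; those do not imply a sicker patient. The text does not say that comorbidity decides treatment.
- **The illustration is unconditional.** Only imbalance remaining after matching counts, and comorbidity probably acts less on cardiovascular death than on death from any cause. Both would make the true bias smaller than the table suggests.

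The Protocol overview also concedes that balanced arms would be hard to define. That acknowledges the difficulty but does not deal with it.

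**Conclusion.** The point holds in a limited form. Matching exactly as written leaves unbalanced a characteristic that the protocol itself links to RFA feasibility, in a non-randomised comparison on cardiovascular survival. The bias probably runs against VT-ART. Its size cannot be derived from the documents. The range of 1.07 to 1.57 for a null effect rests wholly on assumed prevalences and hazard ratios and takes no account of the matched factors, so its upper end should not be read as an estimate.

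It would go too far to conclude that VT-ART patients are sicker than their controls, or that the result will be wrong. The documents support only that they can be sicker and that the matching lists would not prevent it.

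**What to change.** - Abstract from the chart, at the index procedure and in both groups, a comorbidity index (for example Charlson) and renal function. If the CRF already holds them, only the analysis text needs to change.
- Name them as prespecified covariates in the cardiovascular survival comparison, in both the all-factor and the mandatory-only analyses. Keep the terms few, given 49 VT-ART patients. Do not add them as exact-match factors, because the protocol already expects full matching to be difficult.
- Report their balance between groups, with a sensitivity analysis for residual unmeasured confounding.
- Use baseline NT-proBNP only in a sensitivity analysis where it is available. Outcome measures names it as an outcome, and nothing shows that retrospective controls have a baseline value.
- Do not adjust for the reason RFA was not repeated. It is undefined for controls at their index RFA, and for VT-ART patients it nearly encodes treatment.

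The cost is at most a few data fields and model terms, some chart abstraction, and missing values to handle in retrospective controls.
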